# Comparing the Feasibility of In-Person and Online Preventive Cognitive Therapy for Major Depressive Disorder After Partial Response to Repetitive Transcranial Magnetic Stimulation: Protocol for a Pilot Randomized Controlled Trial

**DOI:** 10.2196/101839

**Published:** 2026-09-25

**Keywords:** major depressive disorder, depression, preventive cognitive therapy, relapse prevention, repetitive transcranial magnetic stimulation, experience sampling methodology

## Abstract

**Background:**

In recent years, repetitive transcranial magnetic stimulation (rTMS) has become a first-line recommendation in the Netherlands for individuals with major depressive disorder (MDD) who have not responded to a minimum of 2 prior treatments. Although rTMS can be effective, there is a significant risk of relapse after treatment. Currently, there are no standardized treatment options available after rTMS treatment completion aimed at preventing relapse. Preventive cognitive therapy (PCT) is a brief psychological intervention designed to prevent relapse in partially and fully remitted individuals with MDD.

**Objective:**

This study aims to establish the feasibility of 2 distinct forms of PCT (online and face-to-face) after intensive rTMS treatment for responding patients.

**Methods:**

Participants who demonstrate partial or full response to rTMS, defined as at least 25% reduction in symptoms, as quantified using the Inventory of Depressive Symptomatology–Self-Report (IDS-SR) or an IDS-SR score of 22 or lower will be included. Twenty participants will be randomly allocated to either face-to-face or online PCT, and treatment adherence will be compared between face-to-face and online treatment. The study will be deemed feasible if at least 75% of participants complete PCT during the grant duration of 1.5 years. For PCT, we aim to see which delivery format is the most feasible. Secondarily, changes in affective states, assessed through experience sampling data during PCT, will be studied to establish usefulness for a larger randomized controlled trial aimed at evaluating the effectiveness of PCT after rTMS. Finally, possible MDD relapse will be monitored throughout the intervention and follow-up periods.

**Results:**

This study was funded in November 2023 by the Netherlands Organisation for Health Research and Development. It was reviewed and approved according to the Medical Research Involving Human Subjects Act (*Wet Medisch-Wetenschappelijk Onderzoek met Mensen*) by the Medical Research Ethics Committee of Amsterdam University Medical Center on June 17, 2024. Data collection started in August 2024 and ended in April 2026, with an inclusion of 11 participants. As of June 2026, data analysis has not yet started. We expect data analysis and manuscript preparation of results to be completed in December 2026.

**Conclusions:**

If this pilot study shows preferred feasibility of a specific format of PCT (either online or face-to-face) following rTMS treatment for depression, a larger-scale randomized controlled clinical trial may be performed to study the effects of PCT on remission duration, relapse rates, and affective states in remitted individuals with MDD after rTMS treatment using this preferred delivery format. This pilot will provide insights into the feasibility of face-to-face or online PCT after successful rTMS treatment in depression.

## Introduction

### Background

In 2015, more than 300 million people experienced major depressive disorder (MDD) [1]. This number has increased in recent years, partly due to COVID-19 [2]. Furthermore, in the Global Burden of Disease study of 2023, depressive disorders were in the top 3 causes of years lived with disability [3]. Common treatment options for MDD include psychological and pharmacological interventions. However, approximately 30% to 55% of patients with MDD receiving treatment have treatment-resistant depression (TRD) and, thus, do not meet remission criteria [4,5]. In addition to treatment resistance, recurrence and relapse pose another challenge. Experiencing a depressive episode increases vulnerability to relapse (40%-90% of individuals with a depressive episode relapse), and this vulnerability only increases after multiple episodes of depression [6]. Research has shown that fluctuations in positive and negative affect, especially reductions in positive affect, can predict depressive symptomatology up to 6 months after remission [7]. Notably, the 1-item visual analog mood scale outperformed the widely used 17-item Hamilton Depression Rating Scale (HDRS-17) or Inventory of Depressive Symptomatology–Self-Report (IDS-SR) in predicting relapse over 2 years [8]. This suggests that measuring affect fluctuations using experience sampling methodology (ESM) may be useful in predicting relapse after remission and may help assess the effectiveness of relapse prevention strategies.

### Current Treatments for Remaining in Remission After rTMS

Combining neurobiological and psychological interventions in a multimodal treatment approach is more effective than offering these interventions separately, as shown in previous research. For example, adding a psychological intervention after successful antidepressant treatment has proven to reduce relapse and recurrence rates [22,23]. In rTMS, high relapse rates may be altered by adding psychotherapeutic interventions, as is the case in pharmacological approaches. Earlier studies have shown that combining rTMS treatment with CBT in depression leads to enhanced treatment outcomes [11,24,25]. However, it has not yet been studied whether psychotherapy can sustain the antidepressant effects of this neurobiological treatment. Adding psychological interventions after successful rTMS treatment may lead to a reduction in MDD relapse and recurrence.

Currently, there are no standardized treatment options available to maintain remission after rTMS treatment and prevent relapse. However, some studies have investigated maintenance rTMS and found better effects in comparison to antidepressant monotherapy [24] and sham rTMS [25]. As a review indicates, patients prefer psychotherapy over antidepressant medication as a form of relapse prevention [26]. Therefore, it is important to investigate psychotherapeutic interventions as a means to potentially sustain the benefits of rTMS treatment. A recent meta-analysis found that preventive cognitive therapy (PCT) can reduce depressive symptoms in partially recovered patients when applied immediately after psychological treatment, as well as reducing relapse risk over 12 months [27-29]. Even patients more at risk at baseline were found to benefit from these interventions [27]. Thus, these strategies may also be effective as a relapse prevention strategy after successful rTMS.

### The Potential of PCT After Successful rTMS Treatment

Research has shown that the meta-plasticity caused by rTMS treatment improves response to subsequent psychological treatment [30,31]. This creates an optimal opportunity for preventive therapies such as PCT to reduce relapse rates following rTMS treatment. PCT consists of the following three elements [28,29]: (1) identifying dysfunctional beliefs and schemas using specific cognitive challenging techniques that elicit positive fantasy, (2) enhancing and recalling specific autobiographical memories of positive experiences, and (3) creating a personalized prevention plan [28,29,32]. PCT has been studied in several randomized controlled trials (RCTs) and has shown to have protective effects against relapse up to 20 years after administration [22,33-37]. Substantial effects have been found particularly in those who have a high risk of relapse, that is, clients with recurrent MDD or who have remitted partially. When PCT was combined with antidepressant medication in remitted clients with depression with a recurrent profile, the risk of relapse was reduced considerably (41% risk reduction over 2 years) [22]. In addition, PCT has been established as an alternative treatment by replacing long-term (maintenance) use of antidepressants [22]. In one study, after 20 years, the interval between MDD episodes in individuals was significantly longer after PCT, and these participants had 54% less recurrence of episodes when compared to those who underwent treatment as usual [35]. PCT started after partial and full remission has proven to have preventive effects for patients even after receiving other psychological treatment [6,27,33,34,38-43]. To be eligible for rTMS treatment, patients usually have to have a long treatment history, including different pharmaceutical treatments and CBT, without substantial response [44]. Therefore, PCT seems to be suitable to administer to patients who have received rTMS due to its demonstrated effect in partial remission and the effectiveness after other treatment options [44,45]. As PCT and rTMS target similar patient groups and the meta-plasticity induced by rTMS enhances treatment response, this creates a unique opportunity to prolong the effects of rTMS in remitted patients. Normally, when remission of MDD is reached, PCT is provided 10 weeks after being in remission at the earliest [33,46]. However, we suspect that, if PCT is provided immediately at the end of rTMS treatment to (partial) responders, patients will be more likely to maintain and prolong their remission period due to the meta-plastic benefits directly after rTMS [21].

A major concern of combining PCT with rTMS is the intensity of treatment. rTMS is usually provided daily during several weeks before producing effects. Moreover, some patients finally experience effects after a long treatment history. Therefore, adding 8 weekly sessions to this intensive treatment period may be experienced as a burden. We will study the feasibility of combining PCT with rTMS either face-to-face or online, and treatment adherence will be measured to determine the best treatment delivery for these patients. Previous research has shown that online CBT is as effective as face-to-face treatment [47-49]. Brouwer et al [41] have indicated that online-delivered PCT is also effective. However, online PCT may be viewed as less pleasant due to the lack of personal contact with the therapist, whereas face-to-face delivery may constitute an additional burden after intensive treatment.

### Objectives

On the basis of these previous studies, the primary objective of this pilot study is to compare feasibility and adherence to treatment between online and face-to-face PCT to minimize dropout in a larger RCT. Secondary objectives are to explore the effects of offering PCT to patients who (partially) responded to rTMS treatment on affect fluctuations and remission periods, and study the potential benefits of these measurements for a larger trial.

## Methods

This protocol is reported in accordance with the SPIRIT (Standard Protocol Items: Recommendations for Interventional Trials) guidelines [50].

### Study Design

This study is a pragmatic monocenter RCT with a 1:1 parallel-group design. Twenty patients with MDD who (partially) responded to rTMS treatment will be randomized to either face-to-face or online PCT. This sample size was selected based on practical feasibility in terms of the number of patients with MDD receiving rTMS treatment in Amsterdam, the Netherlands. PCT will be offered as soon as possible after the last rTMS session. Throughout the course of PCT, all patients in both conditions will receive 8 weekly individual sessions (either online or in person) and will be asked to fill out a daily short-form questionnaire. Patients will be assessed before PCT (baseline), directly after PCT (after treatment), and 3 and 6 months after baseline. Total participation duration for the study will be approximately 6 months, as shown in Figure 1. Table 1 provides an overview of the study assessments.

**Figure 1. F1:**
[figure not shown]
Study flowchart. ORS: outcome rating scale; PCT: preventive cognitive therapy.

**Table 1. T1:** Overview of the study assessments. All assessments will be conducted online or via telephone. Some assessment timings overlap and are therefore only shown once.

Assessments	Time investment (min)	Before baseline measurement	Baseline	Daily assessment or administered during treatment	Directly after treatment (±8 weeks)	3 months after baseline	6 months after baseline
Initial screening	10	✓					
Affect short-form questionnaire	60 in total			✓ (5 times a week)			
HDRS-17^a^	5‐20		✓		✓	✓	✓
IDS-SR^b^	10‐20		✓		✓	✓	✓
ORS^c^	10‐20			✓ (weekly)	✓		

a HDRS.17: 17-item Hamilton Depression Rating Scale.

b IDS-SR: Inventory of Depressive Symptomatology–Self-Report.

c ORS: outcome rating scale.

### Recruitment

Patients will be recruited at the outpatient clinic of Amsterdam University Medical Center (UMC; location Academic Medical Center). Other rTMS treatment facilities in Amsterdam can refer potential participants to the study if they meet the inclusion criteria of (partially) responding to rTMS treatment. Data collection will take place at Amsterdam UMC in person or via phone or video call based on the preference of the participant mentioned at previous assessments. Preference will be recorded.

### Participants

Eligible patients must be aged at least 18 years and have (partially) responded to rTMS treatment. We define response or remission as having an IDS-SR score of 14 or lower or a 50% reduction in IDS-SR score. Partial response is determined by an IDS-SR score between 14 and 22 or a reduction between 25% and 50% in IDS-SR score. Patients need to be able to speak and understand Dutch. There are no predefined exclusion criteria as only a select number of patients are found eligible for rTMS.

### Informed Consent and Eligibility Assessment

Patients interested in the study may contact the study researchers directly or give consent to their health care providers to forward their contact details to the researchers. Eligibility screening will be conducted by treating psychiatrists, therapists, or health care providers. Patients will be deemed eligible if they show at least partial response on the IDS-SR (ie, score lower than 22). Prior to participation, potential participants will be provided with detailed information about the study and given 3 days to consider their consent, as requested by the Medical Research Ethics Committee (MREC). Written informed consent will be obtained prior to enrollment and participation in the baseline assessment. The baseline assessment will consist of both clinician-rated and self-report questionnaires. If the participant completes the HDRS-17 and IDS-SR for rTMS treatment within 2 weeks before the baseline assessment, the scores obtained will be used for the baseline assessment instead of administering the IDS-SR and HDRS-17 during this study visit. When the baseline assessment is completed, randomization will take place using a randomization tool in Castor. All participants in the study will be insured by the facility in case of adverse events connected to study participation.

### Intervention: PCT

All participants will receive 8 weekly individual PCT sessions with a duration of 45 minutes each administered by a trained licensed therapist from Amsterdam UMC. PCT is based on the model by Beck [51] and specifically designed for relapse prevention [28,29,42]. Each session consists of a structured format, starting with homework review and explanation of the sessions’ rationale and ending with homework assignments. Homework is an essential part of the therapy and will take 10 minutes each day at most. The treatment is based on the PCT manual [27-29,32].

The number of attended sessions, the overall time taken by the sessions, and whether homework was done will be monitored. All concomitant care will be allowed during the intervention, but if patients are no longer in remission during treatment, they will be noted as relapsed and withdrawn from the study and then referred to their treating psychiatrists for further treatment options. The date of relapse will be noted and used in the analysis of our secondary outcomes.

### Randomization and Blinding

In total, 20 participants will be randomized with a 1:1 allocation ratio to PCT online or face-to-face. A computer-generated randomization table with small block sizes stratified by gender will be used by an independent researcher. After randomization has taken place, an independent researcher (who is not blinded to treatment allocation and will not conduct outcome assessments) will contact the participants and related health care professionals to communicate the participants’ treatment allocation to start the PCT sessions. Participants will be instructed not to share treatment allocation with the blinded outcome assessor. This is to ensure that outcome assessors remain blinded until the end of data collection and consequent database lock.

If knowledge of the allocated group is necessary for the safety of the patients or providing medical treatment, unblinding will be performed by the treating psychologist or the previously mentioned independent researcher.

### Outcomes and Timeline

#### Overview

Data collection will take place at baseline (T0), during treatment, after treatment (T1), 3 months after baseline (T2), and 6 months after baseline (T3). Visits will take place either in person at Amsterdam UMC or via phone or video call based on the preference of the participant. All questionnaires except the HDRS-17 are self-reports and will be filled in via Castor Electronic Data Capture. An overview of the outcomes is shown in Table 1.

#### Primary Outcome

Treatment adherence is the main study parameter and will be measured using registrations on presence during sessions and Epic electronic health records. Treatment adherence will encompass the number of PCT sessions followed, number of weeks in which treatment was administered, outcome rating scale of each PCT session [52], and adherence to homework assignments. Adherence to treatment will be promoted by related health care professionals. Feasibility measures of the different PCT formats will include the percentage of questionnaires completed. If there are significant differences in adherence and feasibility measures between the online and face-to-face PCT groups, this study will advise using the delivery format with the highest feasibility and treatment adherence for a larger RCT on efficacy. If there is no significant difference, then we will advise future RCTs to offer both methods and tailor the delivery format to the preference of the participant. The feasibility of the study itself will be based on recruitment and inclusion rate and number. The study itself will be defined as feasible if at least 75% of participants are able to complete PCT after rTMS within the duration of the grant (ie, 1.5 years).

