#### Statistical Analysis of the Primary Objective

For our primary outcome of feasibility of the different PCT formats, no difference in treatment adherence between both intervention groups is hypothesized. The data on PCT sessions followed, outcome rating scale, and homework assignment compliance will be qualitatively described to determine the best possible treatment options for a larger RCT. Missing data (eg, percentage of missed questionnaires) will be included in the description of adherence. The rate of recruitment and completion of therapy will also be qualitatively described as an indicator of feasibility of the study itself.

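### The rule for advising one PCT format needs a significant difference across five measures, but no measure is named as deciding and the primary analysis plans only description

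*Protocol article*

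**What the plan says.** All of this is in the protocol article.

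- **Main parameter (Primary Outcome).** "Treatment adherence is the main study parameter". It is then spelled out as "number of PCT sessions followed, number of weeks in which treatment was administered, outcome rating scale of each PCT session [52], and adherence to homework". That makes four measures.
- **Feasibility by format (same section).** "Feasibility measures of the different PCT formats will include the percentage of questionnaires completed". This is a fifth measure.
- **Decision rule (same section).** "If there are significant differences in adherence and feasibility measures between the online and face-to-face PCT groups, this study will advise using the delivery format". Which of the two formats that means is settled only by saying it is the one "with the highest feasibility and treatment adherence for a larger RCT on efficacy".
- **Other branch (same section).** "If there is no significant difference, then we will advise future RCTs to offer both methods". The choice would then follow what each participant prefers.
- **Analysis (Statistical Analysis of the Primary Objective).** "The data on PCT sessions followed, outcome rating scale, and homework assignment compliance will be qualitatively described to determine the best possible treatment options". Missed questionnaires enter the description of adherence. Weeks of treatment are not mentioned.
- **Size and timing.** Study Design plans 20 participants, a number set by practical feasibility. Results reports 11 recruited, data collection ended in April 2026, and analysis not started as of June 2026.

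**The concern.** The advice on format is the main product of this pilot. A rule that turns on significance needs to say which comparison is tested and what counts as a positive result. Here the rule refers to several measures at once and names no deciding one. It can be read in at least three ways: any one measure differs, an adherence measure and the feasibility measure both differ, or all of them differ. The article does not choose between these.

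The analysis section serves the same decision with no test at all and a slightly different list. Questionnaire completion also moves from feasibility to adherence, which matters if the rule requires both domains to differ. Whoever writes the conclusion can therefore apply either section, and can decide which measure carries the weight once the results are visible. The Discussion expects each format to have its own disadvantages, so it is plausible that the measures will not move together.

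**Working it through.** **No figure to reproduce.** The article gives no alpha, power or calculated sample size.

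**Inputs.**
- Five measures: four for adherence and one for feasibility (Primary Outcome).
- 10 vs 10 as planned (20 at 1:1). For the 11 recruited, 6 vs 5 is assumed because arm sizes are not reported.
- Two-sided 5% per measure is assumed.
- Formats truly identical, normal measures, equal correlation between measures from 0 to 0.8, two-sample t tests (simulated).

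**Reading 1: any one of five is significant.**
- Independent measures: 1 − 0.95^5 = 1 − 0.774 = 22.6%. For the four adherence measures alone: 1 − 0.95^4 = 18.5%.
- Correlated measures: about 21% at correlation 0.3, 19% at 0.5 and 13% at 0.8, nearly the same at 10 vs 10 and at 6 vs 5.
- Exact rank tests are more conservative in small arms. At correlation 0.5 they give 17% (10 vs 10) and 12% (6 vs 5), against single-test levels of 4.3% and 3.0%.

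**Reading 2: at least one adherence measure and the questionnaire measure are both significant.**
- Independent measures: 0.1855 × 0.05 = 0.9%.
- Correlated measures: about 1.4% at 0.3, 2.1% at 0.5 and 3.5% at 0.8.

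**Reading 3: all five are significant.**
- Below 1% throughout. The largest value is about 0.7%, at correlation 0.8.

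**Outright conflict: one measure significantly favours online and another significantly favours face-to-face.**
- Independent measures: 1 − 2 × 0.975^5 + 0.95^5 = 1 − 1.7622 + 0.7738 = 1.2%.
- Correlated measures: about 0.2% to 0.3% at 0.3, below 0.1% at 0.5, and effectively nil at 0.8.

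**Power of a single named measure for a true difference of 0.8 SD (noncentral t, noncentrality = 0.8 / √(1/n₁ + 1/n₂)).**
- 10 vs 10: 0.8 / √0.2 = 1.79 on 18 degrees of freedom, critical value 2.10, power about 40%.
- 6 vs 5: 0.8 / √(1/6 + 1/5) = 1.32 on 9 degrees of freedom, critical value 2.26, power about 22%.

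**The two sections side by side.** The Primary Outcome section needs a significant result on unspecified measures. The analysis section describes sessions, outcome rating scale, homework and missed questionnaires, and names no test. Neither refers to the other, and neither says which prevails.

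**The case against.** **This is a pilot whose output is advice.** Alpha and multiplicity rules are commonly left to an analysis plan, which is not shown here. That stands, and their absence alone is not raised. But the article does publish the decision rule, and the rule as published has no deciding measure.

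**No tests are planned, so a family-wise error rate describes an analysis that the document does not contain.** This is partly right. If the descriptive section governs, the error rates above do not apply. The rule then has a trigger that nothing can activate, and the choice among measures becomes a matter of judgement. The contradiction is part of the defect.

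**The error inflation depends on the reading.** Correct. A reader might infer that the false-preference rate simply is 23%. The text does not support that, because its wording joins adherence and feasibility, and under the stricter readings the rate falls below the level of a single test.

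**Conflict between measures is rare.** Also correct in the sense that matters to the rule. A reader might infer that the measures will often point to opposite formats and so break the rule. Observed differences will often differ in sign by chance, but the rule acts only on significant differences and otherwise defaults to offering both. Opposite significant results occur in about 1% of null trials or fewer.

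**The likelier failure is a missed difference.** With this sample size, defaulting to both formats is more probable than a false preference. That stands, and naming one measure does not cure it.

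**The two lists barely differ.** True: only weeks of treatment is absent from the analysis section, and questionnaires are filed under a different domain. By itself this would be minor.

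**Conclusion.** The point holds as a defect in the decision rule. Five measures feed the format advice and none is named as deciding. The trigger can be read in several ways, and the analysis section provides no test to activate it. The chance of advising a single format when the two are identical runs from under 1% to about 23% according to the reading, and is about 13% to 21% for any one of five correlated measures. These figures assume two-sided 5% per measure, t tests on normal measures and non-negative correlation; exact tests on small arms would give somewhat less. The problem is an ambiguous trigger and a deciding measure that can be picked after the data are seen. It should be corrected before analysis. For a non-confirmatory pilot it does not put the trial itself in question.

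**What to change.** Before any unblinded analysis, and notified to the ethics committee as a protocol modification:

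1. Name one deciding contrast in both sections, for example PCT sessions attended out of 8, in all randomized participants, online minus face-to-face, with its confidence interval.
2. Say how that interval leads to each branch of the advice. This replaces the undefined significance trigger and reconciles it with the descriptive plan.
3. Label weeks of treatment, homework, outcome rating scale and questionnaire completion as supportive and descriptive, state that they neither trigger nor overturn the advice, and use the same list in both sections.
4. Report sessions missed because of withdrawal for relapse separately. The intervention section withdraws relapsed patients from the study, so a raw session count mixes relapse with adherence.

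Sessions attended is an example; another single measure named in advance would also remove the ambiguity.

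**Cost.** Wording only, with no new data or patients. A difference seen only in a supportive measure could no longer drive the advice. The measure would be named after data collection ended in April 2026, which should be disclosed. Power stays low, at about 40% for 0.8 SD with 10 vs 10 and about 22% with an assumed 6 vs 5, so a wide interval should not be read as showing that the formats are equivalent.

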## Results

This study was funded in November 2023 by the Netherlands Organisation for Health Research and Development. Data collection started in August 2024. As of September 2025, participant recruitment has concluded with a total of 11 participants. In April 2026, the last follow-up measures were performed, and data collection ended. As of June 2026, data analysis has not started. We expect data analysis and publishing of results to be completed in the fall or winter of 2026. The study findings will be disseminated through publication in peer-reviewed scientific journals, as well as presentations at relevant platforms such as clinical care meetings where appropriate.

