## Discussion

With this study, we aim to see which of the two PCT formats is preferred in terms of feasibility and treatment adherence after rTMS. The hypothesized findings of this study are that there are no differences in treatment adherence between online and face-to-face PCT as each format has its own disadvantages. For example, online PCT could be experienced as less pleasant due to the lack of personal contact with the therapist, and face-to-face treatment may constitute an additional burden due to traveling to the hospital after intensive rTMS treatment. However, the actual findings of this study will show whether these hypotheses and assumptions are correct. If so, RCTs on the efficacy of PCT should offer both formats to best suit the preference of the participants. Additionally, in the exploratory analysis on the efficacy of different formats of PCT, we expect no differences as online PCT has already shown to also be effective [41] and, for other psychotherapies such as CBT, no differences have been found between treatment delivery formats [47-49]. This would further strengthen the notion that, if there is no difference in adherence or efficacy, the choice of delivery format should be based solely on the preference of the participant. With this study, we aim to elucidate the feasibility of different delivery formats of PCT after extensive rTMS treatment in individuals in MDD remission.

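### The format advice depends on a significance result that the planned analysis does not produce and that 20 or 11 participants could rarely give, and a null result is then read as no difference

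*Protocol article*

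**What the plan says.** Under Study Design, the size is set on practical grounds: "Twenty patients with MDD who (partially) responded to rTMS treatment will be randomized to either face-to-face or online PCT", and "This sample size was selected based on practical feasibility in terms of the number of patients with MDD receiving rTMS treatment in Amsterdam". Under Results, "participant recruitment has concluded with a total of 11 participants".

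Under Primary Outcome, the protocol article lists what counts as adherence ("Treatment adherence will encompass the number of PCT sessions followed, number of weeks in which treatment was administered, outcome rating scale of each PCT session", plus homework) and adds questionnaire completion as a feasibility measure. A two-branch rule follows. Significant differences lead to advice for the better format. Otherwise: "If there is no significant difference, then we will advise future RCTs to offer both methods and tailor the delivery format".

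Under Statistical Analysis of the Primary Objective, the hypothesis is that "no difference in treatment adherence between both intervention groups is hypothesized", and the analysis is descriptive: "The data on PCT sessions followed, outcome rating scale, and homework assignment compliance will be qualitatively described".

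The Discussion says that the findings will show whether the no-difference hypothesis is correct and, if it is, that trials should offer both formats. It continues that "if there is no difference in adherence or efficacy, the choice of delivery format should be based solely on the preference of the participant".

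**The concern.** The primary objective is to compare the formats so that a larger trial loses fewer participants, and the abstract's conclusion foresees that trial using the preferred format. The rule under Primary Outcome is therefore the step that turns the data into the trial's main recommendation. Three things are wrong with it as written.

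1. It needs a significance result, and the analysis section describes no test that would give one.
2. If a test were run, the sample could detect only very large differences, so the advice to offer both would often follow even when one format is clearly harder to complete.
3. The Discussion lets that branch count as evidence that the formats do not differ, with no margin that says how small a difference is small enough.

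A larger trial could then inherit a finding of no difference that the data cannot carry.

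**Working it through.** **The plan's own figure.** There is none to reproduce. The 20 participants are justified by availability, with no alpha, power or effect size.

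**Inputs.** From the article: 20 planned at 1:1, taken as 10 per arm, and 11 recruited. Assumed, because the article does not give them: two-sided alpha 0.05; Fisher's exact test for completion and a t test for a continuous measure; a 6 and 5 split of the 11; true completion rates of 90% versus 60% and 90% versus 50%; standardised differences around 0.8.

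**Step 1: what completion pattern would be significant?** With fixed margins, each table has the hypergeometric probability C(n1,x)·C(n2,y)/C(n1+n2,x+y), and p sums all tables that are no more probable than the one observed.
- 10 per arm, 10/10 versus 5/10: C(10,10)·C(10,5)/C(20,15) = 252/15504 = 0.0163. The opposite tail is equal, so p = 0.033. For 10/10 versus 6/10, p = 0.087.
- 6 versus 5, 6/6 versus 1/5: C(6,6)·C(5,1)/C(11,7) = 5/330, so p = 0.015. For 6/6 versus 2/5, p = 0.061. The pattern 5/6 versus 0/5 also qualifies (p = 0.015).

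**Step 2: chance of significance on completion.** Power = Σ Bin(x; n1, p1)·Bin(y; n2, p2) over all tables with p ≤ 0.05.

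| True completion | 10 vs 10 | 11, better format has 5 | 11, better format has 6 |
|---|---|---|---|
| 90% vs 60% | 15% | 2.6% | 5.0% |
| 90% vs 50% | 30% | 7.0% | 11% |

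The arm split is not reported, so the figures for 11 participants are ranges: 3 to 5% and 7 to 11%. Put the other way, a true 40-point gap would end in the advice to offer both about 70% of the time with 20 participants and about 90% with 11.

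**Step 3: one continuous measure, such as sessions attended.** The noncentrality is d·√(n1·n2/(n1+n2)) with n1+n2−2 degrees of freedom.
- d = 0.8, 10 vs 10: 0.8·√5 = 1.79 against a critical value of 2.10; power 40%.
- d = 0.8, 6 vs 5: 0.8·√(30/11) = 1.32 against 2.26; power 22%.
- Power of 80% needs d = 1.32 with 20 participants or d = 1.91 with 11.

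**Step 4: can a null result show no difference?** For 5/6 versus 4/5 the observed difference is 0.833 − 0.800 = 0.033. The Wilson limits are 0.436 to 0.970 and 0.376 to 0.964. The Newcombe limits are:
- lower: 0.033 − √((0.833−0.436)² + (0.964−0.800)²) = −0.40
- upper: 0.033 + √((0.970−0.833)² + (0.800−0.376)²) = +0.48

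Even identical results of 8/10 versus 8/10 give −34 to +34 points. For a continuous measure the 95% half-width is 2.10·√(1/10+1/10) = 0.94 SD with 20 participants and 2.26·√(1/6+1/5) = 1.37 SD with 11.

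**Step 5: the sections side by side.** Primary Outcome needs a significant or non-significant result. The analysis section supplies a description. The Discussion uses the absence of a difference as confirmation of the hypothesis. The three do not fit together.

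**The case against.** **The word may not be statistical.** Read with the analysis section, significant could mean notable, and then the power figures describe a test that nobody plans. This stands in part: the figures apply only if a test is run. But on that reading the rule has no criterion at all, and the move from no notable difference to no difference still lacks a basis. The sections need reconciling either way.

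**The rule does not always return the same answer.** A reader might infer that significance is almost never reached and that the advice is fixed whatever the truth. The figures do not support that: power is 40% (20 participants) or 22% (11) at 0.8 SD, and 30% at 90% versus 50% completion with 10 per arm. If any one of five independent measures could trigger the rule, the chance of at least one false difference would be 1 − 0.95⁵ = 23%, so the default would be weaker, though for a bad reason.

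**The measures and the size.** A reader might also fault the lack of a lead measure, the inclusion of the outcome rating scale under adherence, or the small sample. The first is detail that an article may leave to the full protocol or the analysis plan. The second would be inferred from the scale's name alone. A pilot sized by practicality is not at fault for being small, and the shortfall to 11 is disclosed.

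**The advice is cautious.** Offering both formats does little harm, the Discussion also leans on cited evidence about online delivery, and the 75% completion criterion for the study itself does not use significance. This stands and limits the severity.

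**Conclusion.** The concern holds as a fault in a stated rule, not as missing detail. The advice is tied to significance, the planned analysis is descriptive, and a null result is allowed to confirm equality. With 20 planned or 11 recruited, significance is unlikely unless the difference is very large: 15% or 3 to 5% of the time for 90% versus 60% completion, and 30% or 7 to 11% for 90% versus 50%. About 1.3 or 1.9 SD is needed for 80% power on a continuous measure. An interval of about -40 to +48 points around near-equal results rules out reading non-significance as no difference.

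These sizes rest on an assumed two-sided 5% level, Fisher and t tests, a 6 and 5 split and the true rates shown. The contradiction between the sections rests on none of them. This should be fixed, but it does not undermine the pilot as a whole: the study-level criterion is untouched and the remedy is wording.

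**What to change.** 1. Delete the significance condition under Primary Outcome, and bring that section, the Statistical Analysis of the Primary Objective and the Discussion into line.
2. Report each adherence and feasibility measure by arm, with the between-format difference and its 95% confidence interval, without a test.
3. State that a result without a clear difference is inconclusive about format. If the advice is then to offer both, say that it rests on preference and practicality and not on shown equality.
4. Claim no relevant difference only if the whole interval lies inside a stated margin. With half-widths near 0.94 or 1.37 SD, this will rarely be possible.
5. Data collection ended in April 2026, and analysis is reported as not started as of June 2026. Label any margin or lead measure chosen now as set after data collection and before analysis, provided that analysis has still not begun.

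Simply advising the format with the higher observed completion is not a safe substitute. If both true rates were 80%, it would name a winner in 78% of trials with 10 per arm and in 91% with 6 versus 5.

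The cost is wording in three sections. The trial gives up the claim that the formats do not differ, which its size could not support.
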